## Abstract

**Introduction:**

Polycystic ovary syndrome (PCOS) is a common endocrine disorder affecting up to 15% of reproductive-aged women, and is characterized by chronic anovulation that leads to irregular menstrual cycles, infertility, and long-term health risks. While acupuncture has been used for ovulation induction in PCOS, existing evidence remains inconclusive due to methodological limitations and clinical heterogeneity of enrolled populations, which have been largely overlooked. This trial aims to evaluate the efficacy of manual acupuncture for improving ovulation in a precisely defined, more homogeneous PCOS subgroup.

**Methods and analysis:**

This is a prospective, multicenter, randomized, sham-controlled trial. A total of 156 participants with PCOS will be randomly assigned at a 1:1 ratio to receive either manual acupuncture (MA) or sham acupuncture (SA). Eligible participants present with spontaneous menstrual cycles lasting 35–60 days and a body mass index (BMI) below 28.0 kg/m², and this trial targets a subgroup of patients with mild-to-moderate ovulatory dysfunction. The intervention lasts 12 weeks and comprises 36 treatment sessions (three sessions weekly), after which participants will enter a 12-week follow-up phase. The primary outcome is the cycle ovulation rate (COR) at Week 12, verified via transvaginal ultrasound. Secondary outcomes include menstrual cycle characteristics, reproductive hormone profile, metabolic parameters, anthropometric measures, quality of life, anxiety and depression, patient global impression of change, and safety outcomes. Intention-to-treat analysis will be performed, and a p-value <0.05 (two-sided) will be defined as the threshold for statistical significance.

**Systematic Review registration:**

https://itmctr.ccebtcm.org.cn/mgt/project/, identifier ITMCTR2025000078

## Introduction

1

Polycystic ovary syndrome (PCOS) is one of the most prevalent endocrine disorders in reproductive-aged women, affecting approximately 5–15% of this population (1). It is characterized by marked clinical heterogeneity, as confirmed by recent large-scale data-driven studies (2, 3). Its diagnosis relies on the Rotterdam criteria, which require the presence of at least two of the following three phenotypes: oligo-anovulation, hyperandrogenism, and polycystic ovarian morphology (PCOM) (4). Notably, the 2023 international evidence-based guideline recognizes serum anti-Müllerian hormone (AMH) concentrations as a validated alternative to ultrasound for defining PCOM (1). Chronic anovulation, the core pathophysiological feature of PCOS, leads to irregular menstrual cycles, inadequate endometrial shedding, impaired fertility, and an elevated long-term risk of endometrial hyperplasia. Women with PCOS frequently experience anovulation or irregular ovulation, significantly impairing their fertility, with an estimated 30–40% of affected women seeking help for infertility primarily due to ovulatory dysfunction (5). Recovering ovulatory function thus represents a core therapeutic target and an essential prerequisite for spontaneous conception. Recently, an international consensus has renamed PCOS as polyendocrine metabolic ovarian syndrome (PMOS) to better reflect its multisystem nature (6). Beyond the reproductive complications, PCOS also confers long-term metabolic and cardiovascular risks, raises healthcare resource consumption, and imposes considerable psychological distress stemming from its clinical manifestations (7).

Current first-line pharmacological treatments for ovulation induction, such as clomiphene citrate and letrozole, are widely prescribed, although their use may be limited by side effects, contraindications, or patient preference for non-pharmacological approaches (8, 9). While lifestyle intervention constitutes the cornerstone of PCOS management, sustained long-term compliance poses a major clinical barrier (10). Consequently, there is growing interest in complementary therapies like acupuncture, which is hypothesized to improve ovulatory function in women with PCOS by modulating the hypothalamic-pituitary-ovarian (HPO) axis (11, 12) and regulating autonomic nervous system activity (13, 14).

Published randomized controlled trials (RCTs) evaluating acupuncture for PCOS-related ovulation induction have produced conflicting and inconclusive results. Prior systematic reviews have concluded that while acupuncture may improve ovulation and menstrual frequency in PCOS, the overall evidence is limited by low methodological quality (15, 16). Discrepant outcomes across independent trials further highlight this clinical ambiguity. Several positive trials enrolled more homogeneous PCOS populations through strict eligibility criteria (e.g., body mass index, hormonal profiles) (17–19). In contrast, the large, well-powered factorial RCT by Wu et al. (2017) (20) detected no significant ovulatory benefit of active over control acupuncture; this neutral outcome was replicated in a separate sham-controlled RCT (21). Notably, Subgroup secondary analyses of the Wu et al. trial further revealed heterogeneous treatment responses across subgroups, suggesting that clinical phenotypic heterogeneity acts as a critical effect modifier (22). Taken together, these data indicate that acupuncture may generate superior ovulatory improvements among clearly stratified PCOS subgroups. To provide a definitive evaluation of efficacy, we conducted a prospective, multicenter, randomized, sham-controlled trial. This study integrates robust methodology with a precisely defined study population to control for both non-specific therapeutic context and clinical heterogeneity, thereby offering a conclusive assessment of whether manual acupuncture can restore ovulation in a targeted patient cohort. This investigation aims to contribute to a more refined understanding of acupuncture’s potential role in PCOS management.

## Materials and methods

2

### Study design

2.1

This is a multicenter, randomized, sham-controlled trial. The design of this protocol adheres to the Standard Protocol Items: Recommendations for Interventional Trials (SPIRIT) guidelines (23). Descriptions of the manual acupuncture and sham acupuncture interventions comply with the Standards for Reporting Interventions in Controlled Trials of Acupuncture (STRICTA) (24) and the Sham Acupuncture Reporting (SHARE) recommendations (25), respectively. Future reporting of the trial results will follow the Consolidated Standards of Reporting Trials (CONSORT) statement (26).

The trial has been registered with the International Traditional Medicine Clinical Trial Registry (registration ID: ITMCTR2025000078). The study protocol and informed consent documents have been reviewed and approved by the Ethics Committee of the China Academy of Chinese Medical Sciences (Approval No.:2024XLW006-2). All participants will provide written informed consent prior to any study-related procedures. All procedures and time frames are displayed in **Figure 1**. In addition, the schedule of enrollment, interventions, and assessments during the study period is shown in **Table 1**.

**Figure 1 f1:**
[figure not shown]
Flow diagram of the trial. PCOS, polycystic ovary syndrome; MA, manual acupuncture; SA, sham acupuncture; ITT, intention-to-treat; PP, per-protocol.

**Table 1 T1:** Schedule of enrollment, interventions, and assessments.

Study period	Screening	Baseline (Week 0)	Intervention (Weeks 1-12)	Post-treatment (Week 12)	Follow-up (Week 24)
Enrollment					
Eligibility Screening	X				
Informed Consent	X				
Randomization		X			
Interventions					
Manual Acupuncture			3 sessions/week		
Sham Acupuncture			3 sessions/week		
Assessments					
Cycle Ovulation Rate				X	X
Menstrual Calendar*	X	X		X	X
Reproductive Hormones (FAI, LH/FSH)		X		X	X
Metabolic Parameters		X		X	X
Anthropometrics (BMI, WC, HC, WHR)		X		X	X
Questionnaires (PCOSQ, SAS, SDS)		X		X	X
PGIC				X	X
Adverse event			Each visit	X	X
Blinding Assessment				X	
Adherence to treatment				X	X

BMI, body mass index; FAI, free androgen index; FSH, follicle-stimulating hormone; HC, hip circumference; LH, luteinizing hormone; PCOSQ, Polycystic Ovary Syndrome Quality of Life Questionnaire; PGIC, Patient Global Impression of Change; SAS, Self-Rating Anxiety Scale; SDS, Self-Rating Depression Scale; WC, waist circumference; WHR, waist-to-hip ratio.

*At Screening, participants recall their menstrual patterns over the prior 12 months to confirm eligibility (cycle length consistently between 35 and 60 days). At Baseline (Week 0), a paper calendar is provided for prospective daily recording thereafter.

### Participants

2.2

Participants will be recruited from six clinical centers across China: (1) Hospital of Acupuncture and Moxibustion of the China Academy of Chinese Medical Sciences; (2) Beijing Chao-yang Hospital, Capital Medical University; (3) Beijing Hospital of Traditional Chinese Medicine, Capital Medical University; (4) The Affiliated Hospital of Shandong University of Traditional Chinese Medicine; (5) Jiangsu Province Hospital of Chinese Medicine; and (6) Hohhot First Hospital. The primary recruitment strategy relies on hospital-based referrals: gynecologists and reproductive endocrinologists at each study center screen outpatient attendees and refer potentially eligible candidates during routine clinical visits. To broaden outreach, study advertisements and informational posters will be posted on the official websites, permitted social media platforms (e.g., WeChat), and in the outpatient departments (gynecology, endocrinology, reproductive medicine) of all participating hospitals. Interested candidates can contact the local study coordinator via a dedicated phone line or online questionnaire to complete an initial eligibility prescreen.

### Inclusion criteria

2.3

Participants will be women diagnosed with polycystic ovary syndrome (PCOS) according to the 2003 Rotterdam criteria (4), after the exclusion of other potential causes of hyperandrogenism or anovulation (e.g., thyroid dysfunction, hyperprolactinemia, congenital adrenal hyperplasia, androgen-secreting tumors). Eligible participants must meet all of the following criteria: (1) aged 21–40 years old; (2) maintained spontaneous menstrual cycles (without hormonal ovulation induction) over the preceding 12 months, with consistent cycle lengths ranging from 35 to 60 days; and (3) provision of written informed consent.

### Exclusion criteria

2.4

Participants will be excluded if they meet any of the following criteria:

Coexisting endocrine or reproductive disorders that could mimic or confound the diagnosis and manifestations of PCOS (e.g., Cushing’s syndrome, congenital adrenal hyperplasia, premature ovarian insufficiency);Major structural or pathological abnormalities of the reproductive tract that could independently affect menstrual cyclicity or fertility (e.g., untreated endometrial polyps, submucosal fibroids, severe intrauterine adhesions, congenital uterine malformations);Use of acupuncture, or any medication/herbal preparation known or suspected to interfere with ovarian function, menstrual cyclicity, or metabolic parameters relevant to PCOS, within the past month;Body mass index (BMI) ≥ 28.0 kg/m²;Currently pregnant or breastfeeding;Coexisting severe systemic diseases (e.g., cardiovascular, hepatic, renal, or psychiatric disorders, malignancy).

### Traditional Chinese medicine pattern differentiation criteria

2.5

TCM pattern differentiation will be performed by the treating acupuncturist after randomization but prior to the first treatment session. The acupuncturists performing the differentiation are not involved in the randomization process. The diagnostic criteria were developed in accordance with the Criteria of diagnosis and therapeutic effect of gynaenecologic diseases and syndromes in traditional Chinese medicine (ZY/T 001.3-1994) (27) and the General revision and development principle for specification of diagnosis and therapeutic effect evaluation of diseases and syndromes in traditional Chinese medicine (ZY/T 10-2024) (28). Four patterns are predefined: Kidney Deficiency, Phlegm-Dampness, Blood Stasis, and Liver Qi Stagnation. Based on the most prominent clinical presentation, each participant will be assigned to one predominant pattern, with supplementary acupoints added correspondingly as detailed in **Table 2**. Detailed diagnostic criteria are provided in **Supplementary Table 1**.

**Table 2 T2:** Intervention protocol for MA group.

Group & component	Acupoint name (code)	Location (based on WHO standard)	Needling details
A. Core prescription (fixed, alternated by session)			
Set A (Supine)	Zhongwan (CV12)	On the anterior midline, 4 cun superior to the umbilicus.	Perpendicular insertion, 0.5–1.0 cun.
	Huangshu (KI16)	0.5 cun lateral to the umbilicus.	Perpendicular insertion, 0.5–1.0 cun.
	Guanyuan (CV4)	On the anterior midline, 3 cun inferior to the umbilicus.	Perpendicular insertion, 0.5–1.0 cun.
	Dahe (KI12)	0.5 cun lateral to CV4 (Guanyuan).	Perpendicular insertion, 0.5–1.0 cun.
	Zigong (EX-CA1)	3 cun lateral to the midline, 1 cun inferior to CV4.	Perpendicular insertion, 0.5–1.0 cun.
	Zusanli (ST36)	3 cun below ST35, one finger-breadth lateral to tibial crest.	Perpendicular insertion, 0.5–1.2 cun.
	Sanyinjiao (SP6)	3 cun directly above the medial malleolus.	Perpendicular insertion, 0.5–1.0 cun.
Set B (Prone)	Shenshu (BL23)	1.5 cun lateral to the lower border of the L2 spinous process.	Perpendicular insertion, 0.5–1.0 cun.
	Zhongliao (BL33)	In the third posterior sacral foramen.	Oblique insertion toward the foramen, 1.5–2.0 cun.
	Taixi (KI3)	Between the medial malleolus tip and Achilles tendon.	Perpendicular insertion, 0.3–0.5 cun.
B. Standardized adjunct points (added per TCM pattern)			
Kidney Deficiency	Supine: Zhaohai (KI6), Taichong (LR3)	KI6: In depression inferior to medial malleolus. LR3: On dorsum of foot, between 1st and 2nd metatarsals.	Perpendicular insertion, 0.3–0.5 cun.
	Prone: Mingmen (GV4), Ganshu (BL18)	GV4: Below spinous process of L2. BL18: 1.5 cun lateral to lower border of T9 spinous process.	Perpendicular insertion, 0.5–0.8 cun.
Phlegm-Dampness	Supine: Fenglong (ST40), Yinlingquan (SP9)	ST40: 8 cun superior to lateral malleolus, 2 finger-breadth lateral to tibia. SP9: In depression inferior to medial condyle of tibia.	Perpendicular insertion, 0.5–1.2 cun.
	Prone: Pishu (BL20), Weishu (BL21)	BL20: 1.5 cun lateral to lower border of T11 spine. BL21: 1.5 cun lateral to lower border of T12 spine.	Perpendicular insertion, 0.5–0.8 cun.
Blood Stasis	Supine: Hegu (LI4), Xuehai (SP10)	LI4: On dorsum of hand, between 1st and 2nd metacarpals. SP10: 2 cun above medial border of patella.	Perpendicular insertion, 0.5–0.8 cun.
	Prone: Xinshu (BL15), Geshu (BL17)	BL15: 1.5 cun lateral to lower border of T5 spine. BL17: 1.5 cun lateral to lower border of T7 spine.	Perpendicular insertion, 0.5–0.8 cun.
Liver Qi Stagnation	Supine: Ligou (LR5), Taichong (LR3)	LR5: 5 cun above medial malleolus, on posterior border of tibia. LR3: On dorsum of foot, between 1st and 2nd metatarsals.	Perpendicular insertion, 0.5–0.8 cun.
	Prone: Ganshu (BL18), Danshu (BL19)	BL18: 1.5 cun lateral to lower border of T9 spine. BL19: 1.5 cun lateral to lower border of T10 spine.	Perpendicular insertion, 0.5–0.8 cun.

To ensure the reproducibility of TCM pattern differentiation, all acupuncturists will undergo a 2-day centralized training workshop covering the diagnostic criteria for the four predefined patterns, followed by a certification examination (≥80% accuracy required).

### Randomization, allocation and blinding

2.6

Eligible participants will be randomly assigned at a 1:1 ratio to either the manual acupuncture (MA) group or the sham acupuncture (SA) group. Randomization will be stratified by the six participating clinical centers to ensure baseline balance across groups. An independent statistician will generate the randomization sequence using SAS software (version 9.4), with randomly permuted block sizes of 2 and 4. This sequence will be implemented and managed through a centralized, web-based randomization system maintained by an independent clinical research organization (CRO), ensuring allocation concealment. After obtaining written informed consent and confirming final eligibility, the site investigator will access the central system. The system will then automatically assign a unique trial identifier and the corresponding treatment allocation (MA or SA). The allocation remains fully concealed from both the investigator and the participant until the moment of assignment, thereby preventing selection bias. Owing to the nature of the interventions, the acupuncturists administering the treatments cannot be blinded. Therefore, this is an assessor- and participant-blinded trial. All efforts will be made to maintain blinding of the participants, outcome assessors, and data analysts throughout the study.

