#### Safety outcomes

2.9.5

All adverse events (AEs) will be actively screened and documented at every visit through physician inquiry and patient self-report. This includes common acupuncture-specific AEs (e.g., local bleeding, hematoma, pain, bruising, fainting, or prolonged post-needling sensation) and general AEs (e.g., dizziness, nausea). The causality, severity, duration, management, and outcome of each AE will be documented in the Case Report Form. A Serious Adverse Event (SAE) is defined as any event that is fatal, life-threatening, requires hospitalization, or results in significant disability, and must be reported to the principal investigator and ethics committee within 24 hours of awareness. The frequency and severity of all AEs will be compared between MA and SA arms at trial completion.

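### Centre-stratified blocks of 2 and 4, with the arm apparently disclosed to the recruiting investigator, allow about 72% of assignments to be guessed, so the claim that selection bias is prevented is too absolute

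*Protocol article*

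**What the plan says.** Everything relevant is in section 2.6 (Randomization, allocation and blinding) of the protocol article.

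- Ratio and strata: "Eligible participants will be randomly assigned at a 1:1 ratio", and "Randomization will be stratified by the six participating clinical centers to ensure baseline balance across groups".
- Blocks: the sequence is generated "with randomly permuted block sizes of 2 and 4". The probability of each size is not given.
- Who triggers the assignment: "After obtaining written informed consent and confirming final eligibility, the site investigator will access the central system". The system then assigns an identifier and the arm.
- The claim: "The allocation remains fully concealed from both the investigator and the participant until the moment of assignment, thereby preventing selection bias".
- Blinding: "the acupuncturists administering the treatments cannot be blinded". Blinding is promised for participants, outcome assessors and data analysts. The investigator who randomises is not on that list.

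Section 2.5 adds that the acupuncturists who make the pattern diagnosis take no part in randomisation.

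**The concern.** A central web system hides the list. It does not hide what earlier assignments at the same centre reveal about the next one. With short blocks inside each centre, the arms are forced back to balance every two or four women, so anyone who remembers the local tally can often tell which arm is due. The section says concealment from the investigator lasts until assignment, and does not say it continues afterwards. The person who decides on eligibility would then be the person who holds the tally.

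At stake is selective or deliberately timed enrolment according to expected response, which concealment is meant to prevent. There is some room for it. Cycle length is confirmed at screening from 12-month recall (Table 1 footnote), and candidates are referred during routine visits (section 2.2). The primary model described in section 2.13 contains centre as a random effect and names no baseline covariate that would offset a prognostic imbalance.

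**Working it through.** The protocol gives no figure for predictability, so there is nothing of its own to reproduce on this point. The sample size (62 per group, 78 after 20% dropout, 156 in total; section 2.12) reproduces and is not affected.

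**Inputs**
- Blocks of 2 and 4, 1:1 allocation, a separate sequence in each of six centres (section 2.6).
- Assumption: the two block sizes are equally likely. Mixes of 1:2 and 2:1 were also tried.
- Assumption: the guesser knows earlier allocations at the centre.
- Assumption: equal recruitment, 156/6 = 26 per centre. No centre targets are stated; 13 to 52 per centre were also tried.

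**Rule:** guess the arm that is behind at the centre; toss a coin when the arms are level. Block sizes need not be known.

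**Step 1. Expected correct guesses in a block of size 2k:** k + (4^k / C(2k,k) − 1)/2.
- Block of 2 (k = 1): 1 + (4/2 − 1)/2 = 1.5
- Block of 4 (k = 2): 2 + (16/6 − 1)/2 = 2.833
- Equal mix: (1.5 + 2.833)/(2 + 4) = 4.333/6 = 13/18 = 72.2%

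At 26 per centre this is 0.722 × 26 ≈ 19 correct guesses, against 13 by chance.

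**Step 2. Where the correct guesses come from.** Take one block of each size, six assignments in all. In the block of 4, the second assignment returns to balance with probability 2/3, so the third is made at balance with probability 2/3 and at a difference of 2 with probability 1/3.

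| Difference between arms before assignment | Expected number of 6 | Share | Guess correct |
|---|---|---|---|
| 0 | 1 + 1 + 2/3 = 2.667 | 44.4% | 50% |
| 1 | 1 + 1 + 1 = 3 | 50.0% | (1 + 2/3 + 1)/3 = 88.9% |
| 2 | 1/3 | 5.6% | 100% |

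Check: 0.444 × 0.5 + 0.500 × 0.889 + 0.056 × 1 = 0.722.

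**Step 3. Sensitivity (simulation, 6,000 sequences per setting).** The rate is 70.5% to 72.1% for centres of 13 to 52 women. At 26 per centre it is 71.3% to 72.7% for block mixes of 1:2 and 2:1. An optimal guesser who knows the block sizes scores no higher overall, but is certain of about 10% of assignments rather than 6%.

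**Step 4. What larger blocks would do.** The same formula gives 4.1 for a block of 6 and 5.329 for a block of 8.
- Blocks 4/6: (2.833 + 4.1)/10 = 69.3%
- Blocks 4/6/8: (2.833 + 4.1 + 5.329)/18 = 68.1% in the long run; about 67% by simulation at 26 per centre

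For the optimal guesser at 26 per centre, moving from 2/4 to 4/6/8 reduces assignments guessable with probability 75% or more from about 55% to 36%, and certain ones from about 10% to 2%.

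**Step 5. No feedback.** If the recruiter does not learn earlier allocations, the rate is 50% whatever the block sizes.

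**The case against.** The strongest objection is that the key premise is inferred. The article does not say what the investigator's screen displays, and a journal article may leave user roles and the handling of block sizes to the full protocol or the system specification. Without disclosure the rate is 50% and the problem disappears. This stands as a limit on the finding. It does not rescue the text, because the section draws its conclusion from concealment that is stated to last only until assignment.

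It can also be said that consent and eligibility precede system access, that eligibility is bounded (cycles of 35–60 days, BMI below 28), and that the outcome is confirmed by ultrasound. These reduce the opportunity but do not remove it. The next arm can be guessed before access, and an objective outcome does not correct for who was enrolled.

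The objection that larger blocks help little is right: 72% falls only to 67–68%. They are therefore the secondary repair.

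Two stronger readings are tempting and not supported. A reader might infer from the concealment sentence that the participant is told her arm, contradicting the participant blinding. That sentence is ordinary wording for concealment before assignment, and the same section says participant blinding is to be maintained throughout. A reader might also infer biased adverse-event enquiry or concomitant-medication decisions. Section 2.9.5 says adverse events are "actively screened and documented at every visit through physician inquiry and patient self-report", but does not identify that physician as the randomising investigator. Section 2.8 gives the site investigator a say on continuing chronic medication, but nothing there shows that this person knows the arm.

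**Conclusion.** The point holds as a risk, not as proof of bias. With centre-stratified blocks of 2 and 4 and a recruiter who knows past local allocations, 72% of assignments can be guessed correctly instead of 50%. About 56% (50.0% + 5.6%) are guessable with at least 89% accuracy, and the other 44% remain a coin toss, so it would overstate the matter to call the whole sequence predictable. The result rests on three assumptions: the investigator learns each arm (strongly implied, not stated), the block sizes are about equally frequent (72% moves by about one point either way under other mixes), and someone tracks the tally. Actual bias would further require that person to act on it. The statement that selection bias is prevented does not follow from the procedure described. This is an inexpensive improvement to make and leaves the sample size unchanged.

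**What to change.** 1. **Main repair.** For future enrolments, have the web system return only the trial identifier to the recruiting investigator and release the arm solely to the treating acupuncturist. This brings the guess rate towards 50%, provided acupuncturists do not pass allocations on to recruiters. If the system already works this way, say so in section 2.6.
2. **Second layer.** Issue a new list for future enrolments without block size 2, using larger varying blocks (for example 4, 6 and 8) that are not disclosed to sites. Alone this is a modest gain. Keeping the sizes secret does not defeat the simple rule of guessing the arm that is behind.
3. **Wording.** Replace the claim that selection bias is prevented with one that the procedure reduces its risk, and state who receives the allocation.

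The cost is a new randomisation list, a user-role setting and a short text change. The statistical price is that within-centre imbalance can reach 3 (block of 6) or 4 (block of 8) instead of 2.
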